**B. Patients starting at stage I** ***N***** = 548 fixed (620 with interims)**					
	**0**	**I**	**II**	**III**	**IV**
**Intervention**	**85**	**5**	**7.5**	**2.5**	**0**
**Control**	**75**	**5**	**10**	**5**	**5**
**C. Patients starting at stage II** ***N***** = 616 fixed (697 with interims)**					
	**0**	**I**	**II**	**III**	**IV**
**Intervention**	**80**	**0**	**17.5**	**2.5**	**0**
**Control**	**70**	**0**	**20**	**5**	**5**

Hypothetical percent in each pressure ulcer score category by treatment arm, for smallest clinically important effects: overall (A), for stage I (B), and stage II (C)

Table 2 gives total sample size for the combined stages in Table 1 (A), varying the number of measurements per subject (10, 20, 40) and varying ICC (0.2, 0.5, 0.8). The ICC is expected to be relatively high, so the recommended minimum sample size is 548 total (274/gp) for the overall treatment effect combining stages 1 and 2. However, since sufficient power is desired for each of the 2 starting strata, stage I and stage II, roughly the same sample size (548) should be achieved for each strata (see Table 2 for stage I and stage II strata). Therefore, a total maximum (accounting for interim analyses) sample size of approximately 1100 patients was recommended for this trial.

**Table 2 Tab2:** Sample size for varying # measurements and ICC. Data = *N* total. Starting with *N* = 668 total observations (Table 1 (A)), what is the required *N* subjects accounting for ICC and expected number of measurements/subject?

Patient sample	*N* measurements per patient	ICC		
		**.2**	**.5**	**.8**
**Combined stages **Table 1** (A) effect**	**10**	*188*	*368*	*548*
	**20**	*162*	*351*	*542*
	**40**	*148*	*344*	*538*
**Stage I start **Table 1** (B) effect**	**10**	174	342	510
	**20**	150	326	504
	**40**	138	318	500
**Stage II start **Table 1** (C) effect**	**10**	196	384	572
	**20**	168	366	564
	**40**	154	358	562

*N* = 668 assumed 1 measurement per patient (Table 1)

*ICC* intraclass correlation

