#### Significance level

The significance level will be 0.05 for all hypothesis testing and will be controlled at 5% across any multiple comparisons using appropriate multiple testing procedures. Two-sided tests for superiority will be used throughout.

For the statistical analysis of clinical course, unstageable injuries will be assigned a score of 3 (equivalent to stage III injuries). If a patient experiences multiple sacral/ischial pressure injury simultaneously, the most severe injury will be used for analysis.

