#### Primary outcome

The primary outcome will be sacral and ischial pressure injury assessed with the SPI instrument score (range 0–4) over time. For the statistical analysis of clinical course, unstageable injuries will be assigned a score of 3 (equivalent to stage III injuries). For ulcers that progress to deep tissue injuries (DTI), these will be assigned a score of the previous ulcer stage plus one. If a patient experiences multiple sacral/ischial pressure injury simultaneously, the most severe injury will be used for analysis. The primary outcome will be based on the combined stage 1 and stage 2 ulcer types.

Patients will be assessed twice daily by the bedside nurse for pressure injury location and stage from study entry to discharge from the hospital or at least 30 days, whichever comes first. This is a standard wound care evaluation protocol for nursing. Wound care nursing specialist consultation staging will be used instead of bedside nursing staging should a discrepancy occur. If SPI scores are available after discharge and within the 30 days, those data will be included in the analyses as well, even if the SPI are healed or at the worst stage.

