### Interim analysis

Interim analyses will be performed at each 25% of the planned enrollment using a group sequential design assessing the treatment effect on the primary outcome for efficacy and futility. We will use a gamma spending function with gamma parameters − 4 for efficacy and − 1 for futility. Stopping boundaries will be statistically non-binding; statistical accommodation for this option was made in the sample size calculations. The decision whether to stop a study at any interim analysis would be made by the DSMB, which would consider not only the statistical boundaries but other information as well. For example, if a futility or efficacy boundary was crossed at the first look, the DSMB might consider continuing the trial to obtain a more precise estimate of the treatment effect.

All data and results will be submitted to the data and safety monitoring board (DSMB) for review on an A versus B basis unless the DSMB requests to be unblinded. The DSMB is made up of physicians from multiple trial sites and a statistician (Additional file 5). The committee will assess any possible safety concerns, efficacy, and futility and advise if discontinuation is warranted and will meet at least yearly. DSMB members are independent from the sponsor and report to and communicate with the IRB and the steering committee.

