### Sample size considerations

Sample size calculations are based on the primary outcome of pressure ulcer score (0–4), measured over time within a patient and assuming a statistical model (mixed effects ordinal regression) which accounts for the within-subject correlation over the repeated measurements. We designed the study to have 90% power at the 0.05 significance level to detect a treatment effect as large or larger than the effect seen in Table 1 (A) (for the combined starting stages I and II). Sample size was estimated based on applying a design effect to a standard 2-group comparison for independent data (i.e., the Wilcoxon Rank Sum test); it incorporates the number of measurements per patient (m) and an assumed intraclass correlation (ICC) to account for within-subject correlation (i.e., multiply standard sample size calculation by 1 + (m-1)ICC) [15].

**Table 1 Tab1:** Minimal clinically important differences in pressure ulcer score

**A. Combined stages I and II** ***N***** = 586 fixed, *****assuming single measurement***** per patient** ***N***** = 668 with interim analysis adjustment**	**Pressure ulcer score (row percent)**				
	**0**	**I**	**II**	**III**	**IV**
**Intervention**	**82.5**	**2.5**	**12.5**	**2.5**	**0**
**Control**	**72.5**	**2.5**	**15**	**5**	**5**

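### The roughly 1100 maximum is justified by adequate power in each starting stage, but the described looks test only the combined outcome, so stage power is conditional and can fall to about 79% (stage I) and 74% (stage II)

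*Protocol article*

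**What the plan says.** The Sample size considerations section powers the trial on the combined stages: "We designed the study to have 90% power at the 0.05 significance level to detect a treatment effect as large or larger than" the Table 1 (A) effect, which gives a recommended minimum of 548. It then adds a second aim: "sufficient power is desired for each of the 2 starting strata, stage I and stage II". About 548 patients are to be reached in each stage, and the section concludes: "Therefore, a total maximum (accounting for interim analyses) sample size of approximately 1100 patients was recommended for this trial".

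Tables 1 (B) and 1 (C) give each stage a fixed size (548 and 616) and a size with interims (620 and 697). The stage rows of Table 2 start from the inflated sizes.

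The Interim analysis section places looks at each quarter of planned enrollment, "using a group sequential design assessing the treatment effect on the primary outcome for efficacy and futility", with gamma −4 efficacy spending and non-binding boundaries. The Primary outcome section settles what is tested: "The primary outcome will be based on the combined stage 1 and stage 2 ulcer types". Stage is a stratification factor for randomization; no quota by stage is described.

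The Abstract and Trial population section give enrollment as 548, in the latter case as a minimum.

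**The concern.** Two rules pull against each other. The doubling is meant to fill each stage to about 548. The stopping rule looks only at the two stages together, and at 1100 that comparison has about twice the patients it needs for 90% power. If the device works in both stages as assumed, the combined test will usually cross its efficacy boundary well before either stage fills. The interim adjustment in the stage sizes belongs to a stage-level sequential test that the article does not describe.

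What is at stake is how stage results are read. The Discussion says the effect will be reported for each stage separately. After an early stop, a non-significant result in one stage could be set against a claim of sufficient power that was not available at that point, and a real benefit there could be discounted.

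**Working it through.** **Inputs from the article.** Two-sided 5% tests ("Two-sided tests for superiority will be used throughout") and 90% power. Base calculation: a "standard 2-group comparison for independent data (i.e., the Wilcoxon Rank Sum test"). Design effect: "multiply standard sample size calculation by 1 + (m-1)ICC". Table 1 distributions. Efficacy spending gamma −4, futility gamma −1, four equally spaced looks, non-binding futility.

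**1. Reproducing the plan's figures.** Tie-corrected Wilcoxon size: N = (1.960 + 1.282)² (1 − Σp̄³) / [3(θ − ½)²], where p̄ is the mean category proportion and θ the probability of a better score, ties counted half.
- A: θ = 0.55625, 1 − Σp̄³ = 0.5318, N = 589. B: 551. C: 619.
- A version using the alternative-hypothesis variance gives 584, 546 and 614. The stated 586, 548 and 616 lie between.
- The sequential design gives efficacy bounds Z = 3.155, 2.818, 2.439, 2.014 and inflation 1.130. B becomes 619 (stated 620), C 696 (stated 697), A 662 (stated 668).
- Patients per required observation at m = 10, ICC 0.8: (1 + 9 × 0.8)/10 = 0.82. Then 668 × 0.82 = 548, 620 × 0.82 = 508 (stated 510), 697 × 0.82 = 572.

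The plan's method is therefore recovered.

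**2. Combined test at 1100.** 1100/0.82 = 1341 effective observations. Expected final Z = 3.2415 × √(1341/586) = 4.90. With looks at 275, 550, 825 and 1100, numerical integration gives cumulative efficacy crossing of 24%, 75% and 97% by looks one to three. About 3% of trials reach 1100.

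**3. Stage-specific power.** At 550 per stage (670.7 effective observations), expected Z is 3.2415 × √(670.7/548) = 3.586 for stage I and 3.2415 × √(670.7/616) = 3.382 for stage II. Always analysing 550 per stage gives Φ(3.586 − 1.96) = 95% and Φ(3.382 − 1.96) = 92%.

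The two stages were then simulated as independent score processes. The combined Z was tested at each look, and each stage was tested at 1.96 at the look where the trial stopped, with futility not enforced. Mean size was about 560 (280 per stage). Power was 79% (I), 74% (II) and 54% for both.

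**4. How far this moves.** Each row changes one condition from the base case.

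| Condition | Stage I | Stage II |
|---|---|---|
| Base: both effects, 50:50, ICC 0.8, m = 10, quarters of 1100, boundaries followed | 79% | 74% |
| ICC 0.5 | 86% | 81% |
| ICC 0.2 | 93% | 90% |
| The stage makes up 30% of patients | 54% | 48% |
| DSMB continues past look 1 | 81% | 76% |
| DSMB continues past looks 1 and 2 | 89% | 84% |
| DSMB continues past all three | 95% | 92% |
| Only that stage benefits | 94% | 92% |
| Planned enrollment is 548 | 62% | 56% |

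At ICC 0.5 or 0.2 power is higher because each patient carries more information, but under 1% of trials then reach 1100. If only one stage benefits, 58% (I) or 63% (II) of trials run to 1100.

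**The case against.** The strongest reply is that the looks do not by themselves stop the trial. Boundaries are non-binding, the DSMB weighs other information, and the article's own example is continuing after a crossing at the first look to gain precision. That stands: a reader might infer that the trial will stop early and that stage power simply is 79% and 74%, and the documents do not support that unconditional reading. But continuing to fill a stage is not a stated reason to go on, and passing the first look alone recovers only about two points.

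Second, the shortfall arises when both stages benefit, which is when separate stage results matter least. If only one stage benefits, the stage-specific aim is nearly met. This also stands, so it would be too strong to say that the design lacks stage-specific power altogether.

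Third, no numerical power target is set for a stage. The 90% applies to the combined effect, and the Discussion makes stage analyses secondary and calls the interaction underpowered. That is fair, but the admission concerns the interaction. It does not withdraw the within-stage aim that is the stated reason for doubling the trial.

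Fourth, looks at quarters of 1100 may not be the plan. The Trial progress section reports 176 recruited and a first look due the following month, which is closer to a quarter of 548 (137) than of 1100 (275). On that reading stage power is lower still.

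Finally, a reader might infer that the 620 and 697 are errors to be deleted. They are correctly computed for a stage-level sequential test, and Table 2's stage rows depend on them. The full protocol is not shown, so its silence on stage-level looks cannot be assumed.

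**Conclusion.** The point holds in conditional form. The article justifies about 1100 by adequate power in each stage, yet the only stopping rule it describes acts on the combined outcome and can end the trial long before a stage fills. Under the plan's own target effects, an equal stage mix, the ICC of 0.8 and 10 measurements behind its 548, looks at quarters of 1100 and boundaries acted on, stage power is about 79% and 74% rather than 95% and 92%. At least one stage would then be non-significant in about 46% of trials (100% − 54%).

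These are not fixed properties of the design. Across the conditions checked, power runs from about 54% / 48% for a stage making up 30% of patients to about 95% / 92% if every crossing is passed over. The largest open question is whether planned enrollment is 548 or 1100. The combined primary comparison is not affected.

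**What to change.** 1. Reconcile the 548 in the Abstract and Trial population section with the 1100 in Sample size considerations, and say which one the quarter looks refer to.
2. In Sample size considerations, replace the implied sufficient power per stage with the power delivered under the combined stopping rule. Give it as a range with its assumptions: effect in both stages or one, stage mix, ICC, number of measurements, handling of crossed boundaries, and planned enrollment. Do not enter 79% and 74% as single values.
3. Keep the 620 and 697, but label them as applying only if each stage had its own sequential test or were always enrolled in full.
4. State that a non-significant stage result after an early stop on the combined effect will not be read as no effect in that stage.

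The cost is wording and a less favourable stated stage-specific power. These changes in themselves require no extra patients and leave the primary test as it is.

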**Methods:**

The Pressure Injury Treatment by Intermittent Electrical Stimulation (PROTECT-2) trial will be a parallel-arm multicenter randomized trial to test the hypothesis that IES combined with routine care reduces sacral and ischial pressure injury over time compared to routine care alone. We plan to enroll 548 patients across various centers. Hospitalized patients with stage 1 or stage 2 sacral or ischial pressure injuries will be randomized to IES and routine care or routine care alone. Wound stage will be followed until death, discharge, or the development of an exclusion criteria for up to 3 months. The primary endpoint will be pressure injury score measured over time.

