### Trial population

We will include a minimum of 548 adult inpatients who meet the following criteria: (1) hospital inpatients, (2) new or established stage 1–2 sacral/ischial pressure injuries, (3) provide written informed consent in English. Consent is given by the patient or their legally authorized representative (LAR). Subjects enrolled via LAR will be themselves consented when able. Consent will be done in person or by telephone by investigators.

Patients with a pacemaker/AICD, active rhabdomyolysis, gluteal skin breakdown, and unstable fractures at risk of displacement by IES will be excluded. Patients with BMI > 40 kg/m^2^ will also be excluded based on concerns about not being able to elicit a reliable contraction of the muscle with the device. Patients with atrial or ventricular wires after cardiac surgery can be enrolled so long as they are not being actively paced or, in the opinion of the treating physician, likely to requiring pacing during the trial. Patients with multiple pressure injuries in higher stages can be enrolled as long as one of the sacral or ischial injuries is stage 1 or 2.

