## Discussion

Pressure ulcers are associated with high national healthcare costs [3] (3) and are associated with an increased mortality [16]. Despite many preventative measures that have been developed with varying success, few treatments apart from routine wound care practices have been developed. With its mechanisms of increasing local blood flow and redistributing pressure away from muscle-bone interfaces, IES has the potential to facilitate healing and retard progression of pressure injuries. The mechanism would also have significant physiologic plausibility for the prevention of pressure ulcers in high-risk patients, but given the relatively low incidence of pressure ulcers in our analysis, the number of patients required in a trial attempting to demonstrate whether the device can prevent pressure ulcers was prohibitive. Given the burden of pressure ulcers on hospital systems, evaluating the device’s utility for acute care hospital-based treatment of new or established pressure ulcers is necessary.

The device used for this trial has been used in animal trials and small human trials evaluating its efficacy. We opted for testing the impact of electrodes placed around the pressure ulcer overlying the gluteus maximus muscle given its being a large muscle group with the potential to recruit increased blood flow to the area around the ulcer. The specific settings used in terms of frequency and amperage range were initially determined by preclinical data and were also used in the animal and human studies conducted before PROTECT-2.

Limitations for the interpretation of the results of this study do exist. Besides electrical stimulation of the gluteal muscles, other factors may have effect on the progression and healing of ulcers including contemporary wound care treatments, different national standards of treatment, different hospital protocols, and differences between ICU and non-ICU care. However, these findings will not bias the findings of the study given the multicentered, international nature of the trial, and testing for interaction for ICU vs. non-ICU enrollment will be done. In addition, combining stage 1 and stage 2 ulcers for the primary analysis will not enable us to assess whether the IES device may be more effective for 1 stage of ulcer versus stage 2. Nevertheless, in secondary analyses, we will test the interaction, although underpowered, between treatment and baseline stage as well as report the effect for each stage separately.

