## Trial progress

This paper is based on the most recent version of the study protocol (i.e., v5.0, 2023-12-29). The first patient was randomized on June 6, 2022. As of December 30, 2023, we have recruited 176 patients across 3 centers in 2 countries. The first interim analysis based on recruitment is anticipated to be completed January 2024.

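### The article gives two unreconciled trial sizes, 548 and about 1100, without saying which one the 25% looks and the re-estimation use; at 548 the stated per-stage power aim is not met

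*Protocol article*

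**What the plan says.** All of these statements stand in the current text of the protocol article:

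- **Abstract, Methods:** "We plan to enroll 548 patients across various centers".
- **Trial population:** "We will include a minimum of 548 adult inpatients".
- **Sample size considerations, text before Table 2:** "the recommended minimum sample size is 548 total (274/gp) for the overall treatment effect combining stages 1 and 2". The next sentence asks for roughly 548 in each stage, "since sufficient power is desired for each of the 2 starting strata, stage I and stage II", and the paragraph concludes that "a total maximum (accounting for interim analyses) sample size of approximately 1100 patients was recommended for this trial".
- **Interim analysis:** "Interim analyses will be performed at each 25% of the planned enrollment", with gamma spending (−4 for efficacy, −1 for futility) and non-binding boundaries.
- **Internal pilot study:** nuisance parameters are reviewed at the first two looks, and the maximum planned size may then be raised. No starting figure is given.
- **Trial progress:** 176 patients had been recruited by 30 December 2023, and "The first interim analysis based on recruitment is anticipated to be completed January 2024".

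**The concern.** A reader cannot tell whether the trial is planned to end at 548 or at about 1100. In a spending-function design the maximum converts a patient count into an information fraction, so it determines when the looks occur and which boundary applies at a given count. It is also the figure from which any re-estimated maximum would be raised. If 548 is the total, the aim of sufficient power in each starting stage has no design behind it. If 1100 is the total, the abstract and the population section are wrong, and a first look in January 2024 comes too early for a quarter of enrolment.

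**Working it through.** **1. Reproduce 548.** Table 1 (A) gives 586 (fixed design) and 668 (with interim adjustment) for one measurement per patient. Table 2 converts observations to patients as N × [1 + (m − 1) × ICC] / m. With m = 10 and ICC = 0.8 the factor is (1 + 9 × 0.8)/10 = 0.82.

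- From 668: 668 × 0.82 = 547.8, i.e. the stated 548.
- From 586: 586 × 0.82 = 480.5.

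So 548 already carries the interim inflation. It is the group-sequential maximum for the combined test, although the text labels it a minimum.

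**2. Reproduce 1100.** One 548 per stage gives 2 × 548 = 1096. The stage-specific entries in Table 2 give 510 + 572 = 1082. Both are about 1100, so 1100 is the total for two separately powered strata and not an interim-adjusted form of 548.

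**3. Look sizes and boundaries.** Gamma(−4) spending at one-sided 0.025 with looks at 25, 50, 75 and 100%, by numerical integration, gives the same efficacy bounds for any total:

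| Look | z bound | Patients if total is 548 | Patients if total is 1100 |
|---|---|---|---|
| 25% | 3.155 | 137 | 275 |
| 50% | 2.819 | 274 | 550 |
| 75% | 2.439 | 411 | 825 |
| 100% | 2.014 | 548 | 1100 |

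What changes is the bound at a given patient count. At about 548 patients it is 2.014 on one reading and 2.819 on the other.

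**4. Which total fits recruitment?** The 176 patients were recruited from 6 June 2022 to 30 December 2023, about 18.8 months, or roughly 9 per month. A first look at 137 had been passed. A first look at 275 needed 99 more patients, nearly a year at that rate. Trial progress therefore fits 548.

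**5. Power within a stage.** Table 2 already includes the interim inflation, so power with n patients in a stratum that needs N for 90% is Φ(3.2415 × √(n/N) − 1.960), where 3.2415 = 1.960 + 1.282. The documents give no stage split. An even split is assumed: n = 274 at a total of 548, and n = 550 at 1100. All rows use m = 10.

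| Total | ICC | Stage I: N needed, power | Stage II: N needed, power |
|---|---|---|---|
| 548 | 0.8 | 510, 66% | 572, 61% |
| 548 | 0.5 | 342, 83% | 384, 78% |
| 548 | 0.2 | 174, 98% | 196, 97% |
| 1100 | 0.8 | 510, 92% | 572, 89% |

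Example, stage I at 548 and ICC 0.8: √(274/510) = 0.733; 3.2415 × 0.733 − 1.960 = 0.416; Φ(0.416) = 0.66.

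The split matters. If a stage supplies 30% of 548 (164.4 patients) or 70% (383.6), the same formula at ICC 0.8 gives:

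- Stage I: √(164.4/510) = 0.568, power 45%; √(383.6/510) = 0.867, power 80%.
- Stage II: √(164.4/572) = 0.536, power 41%; √(383.6/572) = 0.819, power 76%.

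**6. Combined test.** At 548 it has the designed 90%. At 1100, Φ(3.2415 × √(1100/548) − 1.960) is above 99%.

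**The case against.** The best defence is that the working total can be inferred. The abstract and the recruitment figures both point to 548, the primary outcome is defined on the combined stages, and 548 gives that comparison its 90% power with the interim adjustment included. The 1100 is only described as recommended. This is also a condensed article, and exact look sizes may well be in the full protocol. Most of this stands, and it is why the primary design is not in doubt at 548. It does not remove the conflict: the article itself states both totals, and no unseen document can make both the maximum.

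Four stronger readings are tempting, and the documents do not support them.

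- **That 548 is stated as a maximum.** It is called a plan and a minimum. That it acts as the maximum for the combined test follows only from the arithmetic.
- **That the final critical value is left open.** Quarter looks give 2.014 under either total. Even if looks at 137, 274, 411 and 548 were placed on an 1100 scale, the final bound would move only to 1.985.
- **That the type I error is inflated.** Spending all alpha by 548 and testing again at 1100 with z = 2.014 would give a two-sided error of about 7.9%. No section permits this; the Significance level section requires 5% control, and the re-estimation excludes the treatment effect. It is the risk if both totals were used in turn.
- **That the Discussion concedes weak stage-specific analyses.** It says "we will test the interaction, although underpowered, between treatment and baseline stage", which concerns the interaction test. Such a test would be weak at 1100 too: with each stratum at 90% power, an interaction as large as a whole stratum effect has about 63% power (3.2415/√2 = 2.292; Φ(2.292 − 1.960) = 0.63).

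**Conclusion.** The inconsistency is real and needs correcting. Two totals from two different designs stand side by side, and neither is named as the base for the looks or for the re-estimation. The trial appears to be running to 548. On that reading the combined test is sound, but the aim of sufficient power in each starting stage is not met under the ICC that the section itself calls relatively high. The 66% and 61% rest on an even stage split, 10 measurements and ICC 0.8. They rise to about 83% and 78% at ICC 0.5, exceed 90% at ICC 0.2, and move by tens of percentage points with the split, so they should be reported as a range.

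**What to change.** State one planned maximum throughout, and do so before interim results are released.

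**If it is 548:**

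- Call it the planned maximum in Trial population and Sample size considerations in place of the minimum.
- Tie the looks to it (137, 274, 411, 548) and name it as the starting point for re-estimation.
- Delete the sentence recommending about 1100.
- Drop the per-stage power aim, or restate stratum power as a range with its assumptions on ICC, number of measurements and stage split.

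The cost is a wording amendment and a less favourable statement about stage-specific power.

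**If 1100 is intended:**

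- Correct the abstract and Trial population.
- Set the looks at 275, 550, 825 and 1100, and treat 548 as an interim point only.
- Account for any look already taken near 137 in the spending.

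This is a change in enrolment and not only in wording: it roughly doubles the trial, at about 9 patients per month so far.
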